#### Sample size

2.2.2

The sample size was calculated based on a previous study (3) were authors saw a large effect after the intervention (Cohen d’s effect size = 1.15). Given that to date, there are no consensus in the optimal method to analyze microbiome health status, we selected the change on the relative abundance of *Faecalibacterium prausnitzii* and other SCFA (Short-Chain Fatty Acid) producing bacteria after the intervention (12-weeks) as our primary outcome. Nonetheless, this pilot study was powered to detect a more conservative effect size- of 0.9 on *Faecalibacterium prausnitzii* relative abundance after the intervention between experimental groups. Assuming an 80% power, a two-sided significance level of 0.05, we would need a total of 21 participants/group (calculated on GPower version 3.2). With an allocation ratio of 1:1:1 and an attrition rate of 10%, the final sample is of *N* = 69 (*n* = 23/group) participants.

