#### Primary aim

2.4.1

The primary outcome is to assess the change in the relative abundance of *Faecalibacterium prausnitzii* and other SCFA-producing bacteria after the intervention (12 weeks). The change in the relative abundance of *Faecalibacterium prausnitzii* was selected as the primary aim given that, to date, there are no studies of exercise effect on GM nor a consensual marker of microbiome health status in these patients (32), and thus, the preliminary data collected in this study, will help us to refine our sample size and study procedures for a full-scale RCT. In addition, it has been shown that patients with sarcopenia have decreased abundance of this bacterial strain- a known SCFA-producing bacteria, with an important role on systemic inflammation, anabolic resistance, insulin sensitivity, and energy production (5, 15). Secondary outcomes are the change in relative abundance of *Faecalibacterium prausnitzii* at close-out (24 weeks), the change in the relative abundance of the genera Lactobacillus and Bifidobacterium after the intervention and at the end of follow-up.

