### Statistical analysis

2.6

Descriptive and exploratory analyses will be performed, and normality will be assessed using the Kolmogorov–Smirnov or Shapiro–Wilk tests, and if necessary, the data will be transformed for normalization. The differences between the baseline groups will be explored using one-way analysis of variance (ANOVA) or Kruskal-Wallis tests for continuous data and chi-square tests for categorical data.

The intention-to-treat principle will be used for the primary outcome analysis. The main analyses will employ random coefficient linear mixed models for normally distributed endpoints or generalized mixed models for non-normally distributed endpoints. Post-hoc analysis with Bonferroni correction will assess differences between treatment factors. Cohen’s d will be used to indicate the effect size, and significance will be set at *p* < 0.05.

Fecal samples will undergo taxonomic analysis, grouped into amplicon sequence variants (ASVs), and summarized at different taxonomic levels. These data will be imported in R for use with the Phyloseq package. Several indices of alpha and beta diversity will be evaluated (i.e., Simpson Index, Shannon-Wiener Index, Bray–Curtis dissimilarity, Unweighted and weighted Uni-Frac for beta-diversity). Principal Coordinate Analysis (PCoA) will be performed to visualize the dissimilarity matrix between all samples and a PERMANOVA on exercise groups will be performed. Analysis of Compositions of Microbiomes (ANCOM) with bias correction will be used to test for differential abundance of individual ASVs at several levels to compare the three exercise groups. We will use the Benjamin– Hochberg corrected significance level of 0.05 to minimize false discovery rate (FDR). For the metabolomics analysis, samples will be normalized by the total ion current and means centered using Pareto scaling. Univariate analysis of variance will be performed on data from both ion modes to identify variations in peak areas between groups at baseline and after the 12-weeks intervention. Partial least squares discriminant analysis (PLS-DA) will be used to detect the most critical discriminant metabolites in each comparison across groups consistent with published guidelines for metabolomics trials (36). Microsoft packages (e.g., Excell), SPSS (version 27) and R (version 4.2.) software will be used to manage and analyze the different data.

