The study primary null hypothesis are: (a) there are no differences in *Faecalibacterium prausnitzii* and other SCFA-producing bacteria after the intervention between groups; (b) there are no differences in *Faecalibacterium prausnitzii* and the other SCFA-producing bacteria after the intervention between the RES + AER group versus the AER group; (c) there are no differences in *Faecalibacterium prausnitzii* and other SCFA-producing bacteria after the intervention between the RES + AER group vs. the RES group. We hypothesize that combining AT and RT will have a greater impact on the GM composition, specifically in increasing the relative abundance of *Faecalibacterium prausnitzii* and other SCFA producing bacterial strains, an increase in skeletal muscle mass and strength, as well as enhanced physical performance measures in the concurrent exercise training group.

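### The primary outcome is F. prausnitzii alone in some places and F. prausnitzii plus an unlisted set of SCFA producers in others; only the single species was powered, and no error control is tied to the wider set

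*Protocol article*

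**What the plan says.** The wider definition appears in four places in the protocol article.

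- The Abstract (Methods) pairs *F. prausnitzii* with other SCFA-producing bacteria as the primary outcome.
- Section 2.2.2 (Sample size) chooses the relative abundance of *F. prausnitzii* and other SCFA "producing bacteria after the intervention (12-weeks) as our primary outcome".
- Section 2.4.1 (Primary aim) opens with the change in *F. prausnitzii* "and other SCFA-producing bacteria after the intervention (12 weeks".
- Section 2.6 (Statistical analysis) closes with three primary nulls: (a) across the groups, (b) concurrent versus aerobic, (c) concurrent versus resistance. Null (a) covers *F. prausnitzii* "and other SCFA-producing bacteria after the intervention between groups"; (b) and (c) name the same set.

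The narrower definition appears in two of the same sections. The second sentence of 2.4.1 says that the change in *F. prausnitzii* "was selected as the primary aim given that, to date, there are no studies of exercise effect on GM". In 2.2.2, "this pilot study was powered to detect a more conservative effect size- of 0.9 on *Faecalibacterium prausnitzii* relative abundance".

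On analysis, section 2.6 assigns linear or generalized mixed models to the main analyses, with a Bonferroni step for post-hoc comparisons between treatments and significance at p < 0.05. The next paragraph, on community profiling, adds ANCOM with bias correction, which "will be used to test for differential abundance of individual ASVs at several levels to compare the three exercise groups", under a Benjamini-Hochberg level of 0.05.

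**The concern.** A reader cannot tell in advance which result would reject null (a), (b) or (c). It could be a change in *F. prausnitzii*, in any one of the other SCFA producers, or in some total over them. The two definitions in 2.4.1 stand in consecutive sentences and cannot both be right.

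Two things are at stake. First, the power statement describes one species, so it says nothing about a primary claim that rests on another taxon or on a sum. Second, the Bonferroni step in the mixed models covers treatments, not taxa. If the wider set is primary and its members are tested one at a time, the text as written does not hold the primary error rate at 5%. The article also does not expressly connect nulls (a)-(c) to either the mixed model or ANCOM with bias correction.

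**Working it through.** **Inputs.** From section 2.2.2: effect size d = 0.9 on *F. prausnitzii* (the source study is given as "Cohen d’s effect size = 1.15"), power 80%, two-sided alpha 0.05, 21 per group, 10% attrition, 23 per group and 69 in total. The number of primary taxa, K, is not given; values of K below are assumptions.

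**Step 1: the plan's own figure.** For a two-group comparison of means, the normal approximation gives n = 2(1.96 + 0.84)²/0.9² ≈ 19.4, so 20 per group. The exact two-sided t-test uses noncentrality d√(n/2). At n = 21 this is 0.9 × √10.5 ≈ 2.92 on 40 degrees of freedom, and power is 81.2%; at n = 20 it is 79.2%. So 21 per group reproduces exactly as one comparison of two groups on one taxon at the full 0.05. A three-group ANOVA does not give 21: it needs 17 per group with f = 0.45, or 25 with the smallest f for a range of 0.9. For attrition, 21/0.9 = 23.3; the stated 23 per group leaves 20.7 after 10% loss, which is immaterial here. Nothing in the calculation is reserved for further taxa.

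**Step 2: error rate if taxa are tested separately without correction.** For K independent taxa, all null, each at 0.05, the chance of at least one false positive is 1 − 0.95^K.

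**Step 3: power if Bonferroni were applied over K taxa.** This is the same t-test with alpha = 0.05/K, d = 0.9 and 21 per group.

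| K (assumed) | Any false claim, uncorrected | Power per taxon, alpha 0.05/K | n per group for 80% |
|---|---|---|---|
| 1 | 5.0% | 81.2% | 21 |
| 3 | 14.3% | 66.2% | 28 |
| 5 | 22.6% | 58.7% | 31 |
| 10 | 40.1% | 48.6% | 35 |

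**Step 4: what remains with *F. prausnitzii* as sole primary taxon.** One unadjusted contrast has 81.2% power at 21 per group. With Bonferroni over the two contrasts in (b) and (c) (alpha 0.025), power is 72.0% and 80% needs 25 per group. Over all three pairs of arms (alpha 0.0167), power is 66.2% and 80% needs 28 per group.

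**The case against.** The strongest reply is that section 2.6 is layered. The mixed models follow directly on the sentence about the primary outcome analysis and are called the main analyses. ANCOM with bias correction sits with diversity indices, ordination and PERMANOVA. On that reading the mixed model serves the primary outcome and ANCOM serves broad profiling. This is the more natural reading. A reader might infer that *F. prausnitzii* has two competing primary p-values, but the article does not say so, and using Bonferroni for contrasts and false discovery control for taxa is not wrong in itself. What stands is that the link between nulls (a)-(c) and one method is left implicit.

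A second reply is that the percentages need not describe this trial. The primary wording could mean one summed abundance, in which case there is no multiplicity across taxa. Under Benjamini-Hochberg, with independent taxa that are all null, the chance of any false claim stays at about 5%. This reply is correct, and it limits the figures to separate, uncorrected tests on the mixed-model route.

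A third reply is that this is a condensed article, and a taxon list and an aggregation rule may sit in an unseen analysis plan. That is fair: a reader might infer that taxa will be picked after the data are seen, but the article cannot show that no list exists. Even so, no such plan could make both sentences in 2.4.1 true.

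Finally, the trial is a pilot meant to refine a larger one. That limits the harm, but the article states a power calculation, a significance level and formal primary nulls, and a later sample size also needs one defined outcome.

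**Conclusion.** The point holds as an inconsistency in the definition of the primary outcome, together with a gap in what section 2.6 ties to it. The Abstract, 2.2.2, the first sentence of 2.4.1 and nulls (a)-(c) use an open set; the second sentence of 2.4.1 and the power statement use *F. prausnitzii* alone. No correction across primary taxa is stated for the mixed models.

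The 14%, 23% and 40% for 3, 5 and 10 taxa rest on an assumed number of taxa, separate tests at an uncorrected 0.05, and independence. Correlation between taxa lowers them. They should not be read as the trial's actual error rate.

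Two further inferences are not supported. The sample size arithmetic is not wrong: 21 per group is right for one taxon and one unadjusted contrast. And settling on one taxon would not give one primary p-value, because nulls (a)-(c) would remain. The change should be made before outcome data are seen.

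**What to change.** Make the change in *F. prausnitzii* relative abundance at the end-of-intervention visit the sole primary outcome, in the same words in the Abstract, 2.2.2, 2.4.1 and nulls (a)-(c). Move the other SCFA producers to a fixed, named secondary list under Benjamini-Hochberg. State in 2.6 that the mixed model decides the primary hypotheses and that ANCOM with bias correction is supportive. This choice matches the sample size basis and the reason given in 2.4.1. Listing the taxa as primary and controlling error across them would also be valid, but at 21 per group it costs the power shown in the table.

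The change removes multiplicity across taxa only. The contrasts in (a)-(c) still need the Bonferroni step already stated, and the power statement should say that about 81% applies to one unadjusted contrast and about 72% with Bonferroni over two.

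The cost is wording and a registry update. The downside is that other SCFA producers can no longer carry the primary claim.

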## Discussion

3

To date, there are no studies on the effects of exercise on GM nor a consensual marker of gut microbiome health status in older adults with sarcopenia. This paucity of data and the scarcity of evidence limits, not only the clinical application of the optimal exercise prescription regimen in clinical context but also by exercise specialists among these high-risk patients. The existence of the gut-muscle axis adds a novel dimension to our understanding of the pathophysiological mechanisms of sarcopenia and raises the attractive possibility that by manipulating the GM composition and function, we could mediate changes in beneficial bacterial taxa associated to skeletal muscle health (e.g., *Faecalibacterium praunitzii*) and prevent sarcopenia and its adverse health outcomes (37).

The increasing prevalence of sarcopenia demands effective treatment interventions to alleviate the personal, social, and economic burden associated with this condition. It has been estimated that a reduction of sarcopenia by 10% in the US healthcare system would save up to $ 1.1 billion per year. Thus, our study will contribute to this specific goal by evaluating the impact of different exercise training regimens on a new emerging regulator of skeletal muscle mass and function (i.e., gut microbiome) which has been linked to functional impairment. Our study will expand the current knowledge in this area and will provide precise information to prescribe the optimal treatment plan in these patients, stimulating an active intervention to preserve people’s autonomy. In addition, this project will provide the preliminary data to further investigate other underlying unknown mechanistic links that mediates different exercise training modalities and contribute to a consecutive line of research aimed at unraveling the role of gut microbiome and its multiple interaction mechanisms in exercise training in patients with sarcopenia.

Aging decreases dominant species such as *Bacteroidaceae*, *Lachnospiraceae*, and R*uminococcaceae* and increases subdominant species, particularly, opportunistic bacteria (38). Several studies correlate changes in the diversity of the GM with poor physical performance in older adults, and an increase in the representation of *Faecalibacterium prausnitzii, Roseburia inulinivorans*, and *Alistipes shahii* in the feces of non-sarcopenic people compared to sarcopenic stools (5, 39). The abundance of *Faecalibacterium prausnitzii*—known for its important role in the health of the gut microbiota (i.e., in insulin sensitivity, anabolic balance, and inflammation), appears in some studies with a representation up to 5 times lower in individuals with sarcopenia (5, 18). *Bifidobacteriaceae, Dialister, Pyramidobacter* and *Eggerthella* and the depletion of *Slackia* and *Eubacterium* were also increased in older adults with physical frailty and sarcopenia, when compared to non-frail individuals (40). Therefore, therapeutic strategies developed to modulate GM composition may have clinical meaningful implications in age-related muscle loss and physical function decline.

While research into sarcopenia treatments (nutraceuticals to pharmacological strategies) surged over the past decade, only physical exercise, especially RT (27), alone or in combination with AT, was proven effective in enhancing health outcomes and functionality in older adults (41). Clinical studies also show that combining exercise with dietary supplements (protein or fiber) effectively fights sarcopenia (42). Whether these changes in patients with sarcopenia are paralleled by modifications of GM remains to be explored.

A recent review summarizing data from interventional and observational studies on older adults (where sarcopenia was more prevalent) indicated that exercise and physical activity can have a beneficial impact on the GM composition (19) but due to methodological and sampling disparities, it was not possible to reach a consensus on which taxa was most responsive/influenced by exercise. Further, growing evidence shows that different exercise training modalities (type, frequency, duration, and intensity) may elicit different GM composition phenotypes and skeletal muscle health outcomes (18). Propionate and butyrate, both gut-derived SCFA metabolites, can act as adenosine monophosphate-activated protein kinase (AMPK) activators and stimulate peroxisome proliferator-activated receptor-gamma coactivator 1 alpha isoform (PGC-1α) and insulin/Insulin-like Growth Factor 1 (IGF-1) signaling, promoting muscle biogenesis, whereas its decrease has physiological consequences like reduction in the mitochondrial fatty acids’ oxidation, increased intramuscular fatty acid deposition and insulin resistance (1, 11). Thus, given that different exercise training regimens differently impact the body, we can hypothesize that each regimen promotes distinct alterations on GM composition. RES may enhance bacterial strains associated to muscle strength while AER may promote the increase on the relative abundance of taxa associated to aerobic capacity and SCFA production whereas the combination of both forms of exercise (resistance + aerobic) may lead to an added effect. Furthermore, with this study we will be able to shed light on the (ir)reversibility of the preliminary results, evaluate the adequacy of our primary outcome and analyze the effect of our intervention. The findings collect on the washout period will be important to investigate GM resilience (i.e., the ability or process of the GM to withstand exercise benefits and/or manage everyday challenges) and specifically, explore whether these changes induced by exercise are sustained over time or not in the three different exercise regimens.

*In summary*, with this study we expect to create a consecutive line of research to fill a current literature gap and explore the impact of three different exercise regimens on GM composition and gut-derived metabolites in older adults with sarcopenia. These findings may help clinical guidance and enhance exercise prescription in this high-risk population. For instance, if confirmed that RES + AER are the optimal mode of exercise training to modulate GM composition and improve skeletal muscle health, clinicians and exercise specialists may prioritize it in patients with sarcopenia with certain GM composition phenotypes. Lastly, our study will contribute with an evidence-based approach, to a deeper understanding on the optimal exercise mode to elicit gut and skeletal muscle health benefits. Therefore, our study could have clinical meaningful implications and impact patient’s quality of life and lifespan.

## Data Availability

The original contributions presented in the study are included in the article/supplementary material, further inquiries can be directed to the corresponding author.

## Abbreviations

1RM: one-repetition maximum
AER: Moderate Aerobic Exercise
AMPK: Adenosine Monophosphate-Activated Protein Kinase
ANCOM: Analysis of Compositions of Microbiomes
ASVs: Amplicon sequence variants
AT: Aerobic Training
BMI: Body Mass Index
BW: Body Weight
CERT: Consensus on Exercise Reporting Template
CIAFEL: Research Center in Physical Activity, Leisure and Health
CV: Cardiovascular
DBP: Diastolic Blood Pressure
EWGSOP: European Working Group on Sarcopenia in Older People
FDR: False discovery rate
GM: Human Gut Microbiota
HR: Heart Rate
HR_max_: Maximum Heart Rate
IGF**-1**: Insulin-like Growth Factor 1
IPAQ: International Physical Activity Questionnaire
IPATIMUP: Institute of Molecular Pathology and Immunology of the University of Porto
LC–MS: Liquid chromatography- mass spectrometry
NGS: Next generation sequencing
PA: Physical Activity
PCoA: Principle Coordinate Analysis
PLS**-DA**: Partial least squares discriminant analysis
RCT: Randomized Control Trial
RES: Resistance Exercise
RES + AER: Concurrent Exercise Training
RPE scale: Rate of Perceived Exertion Scale
RT: Resistance Training
SBP: Systolic Blood Pressure
SCFA: Short-Chain Fatty Acids
SPPB: Short Physical Performance Battery
TOF: Time-of-flight
UA: University of Aveiro
UMIB: Unit Multidisciplinary Research in Biomedicine
